##### Non-scheduled coronary intervention

Number of non-scheduled coronary interventions (only first event per patient) divided by number of patientsThe national health registry is used to determine whether the patient has a non-scheduled intervention performed. Time from index admission to first intervention and type of intervention (PCI or coronary artery bypass graft [CABG]) is determined. The endpoint committee adjudicate interventions blinded to original treatment strategy.Will be evaluated when inclusion of all patients is completed

##### Life-threatening arrhythmias

Number of events with life-threatening arrhythmia (only first event per patient) divided by number of patientsThe national health registry is used to determine whether the patient is diagnosed or re-admitted with a life-threatening arrhythmia, defined as ventricular tachycardia, ventricular fibrillation or third-degree (total) atrioventricular block within index admission and within 30, 90 or 365 days of randomization. The endpoint committee adjudicates re-admission with life-threatening arrhythmia, blinded to the initial randomization.Will be evaluated when inclusion of all patients is completed

##### Other outcome measures

ᅟ

##### Diagnostic performance characteristics of the accelerated rule-out algorithm as compared with standard diagnostics

Sensitivity, specificity, positive predictive value and negative predictive value for the diagnosis of AMI will be evaluated in interim analysis after 300 patients have been discharged after rule-out of AMI in each site (patients discharged from hospital within 12 h of admission)

##### Prognostic value of the accelerated rule-out algorithm as compared with standard diagnostics

Mortality within 1, 7, 30 and 365 daysWill be evaluated in interim analysis after 300 patients have been discharged after rule-out of AMI in each site (patients discharged from hospital within 12 h of admission)

##### Cost efficiency

Costs and cost-effectiveness will be evaluated and compared between the two diagnostic strategies.Will be evaluated in interim analysis after 300 patients have been discharged after rule-out of AMI in each site (patients discharged from hospital within 12 h of admission)

##### Risk factors and patient experiences

We plan to evaluate the patients’ experience of being discharged earlier and risk factors for early re-admission.

##### Effect of the accelerated model on each outcome component in the primary outcome

Regression models of each outcome component, including randomization group, age, sex, symptoms, time from onset of symptoms, known co-morbidities, pre-existing ischaemic heart disease, ECG changes, site of inclusion, season, and time since trial start-up

#### Participant timeline

*See* Fig. 1. Patients are enrolled as early as possible after admission. Procedures of importance for acute patient safety will precede the inclusion process. The attending nurse will inform and, if eligible for inclusion, enrol and randomize the patient when relevant acute procedures are completed or initiated. The attending nurse and physician collect baseline information (*see* “Data collection methods” Section).

Patients assigned to the standard group are scheduled to have two consecutive in-hospital hs-cTn measurements with an interval of 3 h. Adhering to the study protocol will result in a minimum admission time of 4 h: initial assessment/treatment + enrolment, allocation and first blood sampling + 3-h interval to second sampling + laboratory turnaround time. Additional treatment and diagnostic procedures (including repeat hs-cTn measurement) are fully at the discretion of the attending physician.

Patients assigned to the accelerated group are scheduled to have one in-hospital hs-cTn measurement performed, which will result in a minimum admission time of 1 h: initial assessment/treatment + enrolment, allocation and blood sampling + laboratory turnaround time. Additional treatment and diagnostics (including repeat hs-cTn measurement) are fully at the discretion of the attending physician. The endpoint committee will assess MACE events within 30, 90 and 365 days (*see* “Data collection methods” section).

### Sample size

The total sample size will be 4800 patients.

#### Sample size calculation

Thirty-day MACE including all-course mortality is expected to be between 5.5% and 7.5% [7, 20]. Using a MACE rate of 6.5%, a non-inferiority limit of 2%, alpha = 2.5% and power (beta) = 80% will result in the need for enrolment of 4772 patients to confirm a difference in 30-day MACE rate of more than 2%.

Regarding LOS, in 2012, the average LOS of patients admitted with suspected AMI at Aarhus University Hospital was 12 h (SD = 6.1). It is expected that 40% of patients in the accelerated group can be discharged within 3 h after admission [7, 20], thus resulting in an estimated 1–1.5 h reduction of LOS in patients discharged without AMI.

Inclusion of about 4800 patients in total will enable us to show a difference in LOS of 54 min with a power > 90%. To show an average 1.5-h reduction in LOS (under the condition that 40% in the accelerated group are discharged within 3 h), 337 patients in each randomization group discharged after early rule-out of AMI (patients discharged from hospital within 12 h of admission) are needed (μ = 12, SD = 6.1, alpha = 5%, beta = 90%). To take differences between sites into account, we increased the number of discharged patients by one-third to 450 patients per randomization group. Distributing the patients equally between sites (150/site/randomization group), 300 patients discharged after rule-out of AMI (patients discharged from hospital within 12 h of admission) in each site are needed.

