### Outcomes

#### Outcome measures

##### Primary outcome measures

LOS:Time (hours and minutes) from admission to discharge from cardiac department (either to home or to a non-cardiac department)Retrieved from the patient administrative system, the patient’s medical record and the national health registryWill be evaluated when 300 patients have been discharged after rule-out of AMI at each site (patients discharged from hospital within 12 h of admission)Combined MACE proportionCombined endpoint of MACE (only first event per patient), consisting of the following (Occurring within time from randomization to 30 days after randomization):All-cause mortalitySurvived cardiac arrestConfirmed acute coronary syndrome (ACS) or re-admission with ACSNon-scheduled coronary interventionLife-threatening arrhythmiasWill be evaluated when inclusion of all patients is completed

(*See below* for detailed description of each component of the combined endpoint.)

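### The length-of-stay sample size for patients discharged within 12 h uses the mean (12 h) and SD (6.1 h) of all admissions, values that cannot occur in stays capped at 12 h

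*Protocol article*

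**What the plan says.** All references are to the protocol article. Under Study design, LOS and MACE are the two primary endpoints.

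Under Sample size calculation, the planning values are introduced as a description of everyone admitted with the suspicion: "the average LOS of patients admitted with suspected AMI at Aarhus University Hospital was 12 h (SD = 6.1"). The expected benefit is a range, "thus resulting in an estimated 1–1.5 h reduction of LOS in patients discharged without AMI". The calculation takes the upper end ("To show an average 1.5-h reduction in LOS") and arrives at "337 patients in each randomization group discharged after early rule-out of AMI (patients discharged from hospital within 12 h of admission"), who "are needed (μ = 12, SD = 6.1, alpha = 5%, beta = 90"%). For site differences, "we increased the number of discharged patients by one-third to 450 patients per randomization group", which becomes 150 per site per group, or 300 per site.

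The same section makes a separate statement about the whole trial: "Inclusion of about 4800 patients in total will enable us to show a difference in LOS of 54 min", with power above 90%. It does not say whose stays are compared.

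Under Primary outcome measures, LOS is to "be evaluated when 300 patients have been discharged after rule-out of AMI at each site". Statistical analysis plans two LOS comparisons: the whole randomised groups, and the subgroups discharged within 12 h. It sets a two-sided 5% level. Hypothesis gives the LOS target as a 12.5% reduction in ruled-out patients. Participant timeline gives minimum stays of 4 h (standard) and 1 h (accelerated) when the protocol is followed.

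**The concern.** The mean and SD belong to one population and the sample size to another, defined by a ceiling on the very variable being compared. The planning mean equals that ceiling. If the inputs cannot occur in the group analysed, the 90% power attached to 337 per group says nothing about the comparison that triggers the LOS evaluation.

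The effect size has a related weakness. The 12.5% target equals 1.5 h out of 12 h, so it appears to rest on the same all-admissions mean. What reduction can appear once stays above 12 h are cut off is a different question. A faster strategy may move patients from just above the cap to just below it, which adds long stays to the accelerated subgroup and shrinks the visible difference.

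At stake is whether a reader can rely on the stated power for one of the two co-primary endpoints, and whether the 54-minute statement can be tied to either planned comparison.

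**Working it through.** **Inputs (Sample size calculation unless noted).** Difference 1.5 h; SD 6.1 h; two-sided alpha 5% (Statistical analysis); power 90% (printed as beta); allocation 1:1 (Intervention groups).

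**1. The plan's own figure.** n per group = 2(z₀.₉₇₅ + z₀.₉₀)² SD² / difference².
- SD 6.1: 2 × (1.96 + 1.2816)² × 6.1² / 1.5² = 347.5, so 348 (349 by t-test).
- SD 6.0: 336.2, so 337. This is the printed number.
- One-sided alpha (284) and 80% power (260) do not give 337.
- Inflation: 337 × 4/3 = 449.3, so 450 is consistent, as is 150 × 2 × 3 = 900. Starting from 348 it would be 464.
- Power for 1.5 h with SD 6.1 is 89.1% at 337 per group and 95.8% at 450.

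**2. Can the inputs occur in stays of at most 12 h?** For a variable confined to [a, b] with mean m, SD ≤ √((m − a)(b − m)), which is never more than (b − a)/2.
- On 0–12 h with mean 12: √(12 × 0) = 0.
- On 0–12 h with any mean: at most 12/2 = 6.0 h, reached only at mean 6 h.
- On 1–12 h (accelerated minimum in Participant timeline): at most 11/2 = 5.5 h.
- On 4–12 h (standard minimum): at most 8/2 = 4.0 h.

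Mean 12 h with SD 6.1 h is therefore impossible in this group. The last two ceilings assume that patients follow the protocol; the first two need no assumption beyond the cap.

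**3. What a feasible SD would imply.** The article gives no SD for this group, so these values are assumptions. For 1.5 h at 90% power and two-sided 5%:

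| Assumed SD (h) | n per group |
|---|---|
| 2.5 | 59 |
| 3 | 85 |
| 4 | 150 |
| 5.5 | 283 |

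As an illustration, a normal or gamma distribution with mean 12 and SD 6.1 cut at 12 h has mean about 7.6–7.8 h and SD about 2.6–3.0 h. Taken alone, the SD error makes 337 too large. The expected difference inside the capped group is also missing, so actual power cannot be computed.

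**4. The 54-minute statement (0.9 h, SD 6.1).** Power = Φ(0.9 / (6.1 √(2/n)) − 1.96).
- n = 2400 per arm: 0.9/0.1761 − 1.96 = 3.15, power 99.9%. The difference detectable with 90% power is 3.2415 × 0.1761 = 0.571 h, about 34 min.
- n = 450 per group, the number at the stated LOS timing: 0.9/0.4067 − 1.96 = 0.25, power about 60%.

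The second line borrows the all-admissions SD. It shows only how much the unnamed population matters and is not an estimate of power in the capped group.

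**The case against.** The best defence is that nothing practical turns on this. The total of 4800 is driven by MACE (4772 patients), an overstated SD errs on the safe side, the 337/348 gap is about 3%, and 450 per group more than covers it. All of that stands, and it is why the gap is secondary. It does not rescue the 90% power: the effect in the capped group is as unsupported as the SD, so the surplus cannot be assumed to offset it.

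A reader might infer more than the document supports:
- **Two conflicting LOS timings or sizes.** Only one LOS timing is stated, at 300 rule-out discharges per site. Evaluation at completed inclusion is attached to MACE and the event outcomes. The 4800 and the 337/450 go with different effects (54 min and 1.5 h), so they do not contradict each other.
- **Inflated type I error.** Testing at 900 and again at 1920 rule-outs would give 8.4%, but no section plans a second LOS test, and the 1920 assumes that 40% of 4800 are ruled out within 12 h.
- **54 minutes really belongs to 40% of the trial.** With 960 per arm, power is 89.8%, which misses the stated claim of more than 90%. With 2400 per arm the claim is true. The fair criticism is only that the population is not named.
- **Real power of 69% for a 1 h reduction.** That figure (450 per group) uses the SD of 6.1 h that the cap rules out. With SDs of 5.5, 4 or 3 h it would be 78%, 96% or 99.9%.

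**Conclusion.** The LOS calculation for patients discharged within 12 h is invalid as written, because its mean and SD cannot occur in that group. This follows from the cap alone. The stated 90% power does not describe this comparison. The actual power is unknown in either direction, so the documents do not support calling the comparison underpowered.

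Two lesser defects stand. The printed inputs give 348 rather than 337 per group, a gap worth about one percentage point of power and covered by the increase to 450. The 54-minute statement is literally true for all 4800 patients at SD 6.1 h, but it names no population, and on the same SD its power would be about 60% with 450 per group.

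The assumptions are a two-sided 5% test, beta read as power, equal group sizes, and the normal approximation for a comparison of means. That the 1.5 h effect derives from the 12 h mean is an inference from 1.5/12 = 12.5%.

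**What to change.** - Attach mean 12 h and SD 6.1 h only to the all-randomised LOS comparison already planned under Statistical analysis, and state its power there: 90% for about 34 min at 2400 per arm.
- For the within-12-h comparison, replace the basis of 337/450 with a mean, SD and expected difference that belong to that population. Restate its size or power, including at the 1 h lower end of the expected range. If no such data exist, withdraw the 90% power. Changing 337 to 348 is not enough, because 348 rests on the same SD.
- Say which of the two comparisons the 54-minute statement describes.

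The cost is a few restated sentences and a power figure that may look less favourable. No extra patients are needed, and the MACE-driven total is unaffected.

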### Recruitment

All study sites have local study representatives and receive regular visits and contacts from the principal investigator (PI) to ensure high local engagement and recruitment. All nurses at the participating departments are trained to perform enrolment of patients.

### Informed consent and assignment of interventions

#### Consent

Patients are enrolled by the attending nurse at presentation. All nurses at the participating departments are trained to perform enrolment of patients.

Information, collection of informed consent, and randomization/allocation are done using the TrialPartner web-based trial system. TrialPartner is accessible from a tablet and has all study information available to support patient information, including the full written information and a study description for study personnel.

The attending nurses will do the following at the time of admission:Inform the patients in both oral and written formCollect signed informed consent to participate in the studyEnter site, personnel ID, patients’ wishes regarding information of results, and patients’ diabetes status (yes/no)Press the randomization–button to determine allocation (*see* “Allocation” section below).

#### Additional studies

In parallel, the nurses will also collect signed informed consent forms from the patients for storage of remaining blood plasma in a biobank (*see* Additional file 2).

#### Allocation

Web-based computer randomization is used to allocate patients to the treatment groups at a 1:1 ratio, stratified by site and diabetes status (yes/no), by the method of permuted block randomization with random varying block sizes. The trial system (TrialPartner) permits, with a personal log-in, 24-h randomization. All actions in the system are logged. Patients are randomized and allocated using a web-based solution from a tablet. The allocator needs to enter the patient’s social security number; present written information; retrieve the patient’s signature on consent (via the tablet); sign the consent (via the tablet); and input site, diabetes status (yes/no) and ID before the web database will allow allocation.

The allocation sequence is generated by a local data manager at Aarhus University and incorporated into the web-based TrialPartner. All information on allocation sequence is blinded to study personnel, including the authors. After allocation, the nurse or other personnel at the department order blood sample packages according to allocation (*see* “Sample request and reporting” section).

### Blinding

The AROMI study is by design an open, unblinded study because disclosure of the assigned group and associated blood sampling should enable an altered patient management. Members of the endpoint committee will be blinded to allocation. Because the committee will have full access to patient file information from the cardiac departments, there will be cases where the allocation will be revealed or appear obvious to the committee members.

### Data collection, management and analysis

#### Data collection methods

Raw data are collected from several sources, outlined below.

##### Case report form

The attending personnel complete a case report form (CRF) in which baseline characteristics, symptoms and ECG at presentation, clinical evaluation, time of admission and time of discharge, presumed MACE during admission, and diagnostic procedures during admission are documented.

##### Patient medical record

Missing or non-reported data regarding baseline characteristics, symptoms and ECG at presentation, and diagnostic procedures are supplemented from the medical record. To ensure uniformity, the supplementation is performed by three trained assessors. Medical records are also used for identifying suspected MACE events (*see* “Adjudication of events” section).

##### Laboratory information management system

Data on blood sampling, including date and time of blood sampling, name and Nomenclature for Properties and Units code of the analyses, and results are retrieved from the laboratory information management system (LABKA).

##### Registries

Data are retrieved from several registries. Registry data are used for supplementing missing or non-reported data regarding baseline characteristics and for identifying suspected MACE events (*see* “Adjudication of events” section). The list of registries and registry data used can be found in Additional file 3.

#### Endpoint committee adjudication

The endpoint committee will adjudicate MACE endpoints and report these electronically to the PI (*see* “Adjudication of events” section).

#### Data material

We will collect data on the following groups of measures (*see* Additional file 3 for further specification):

Outcome data:LOS: derived from time of admission and time of dischargeMACE events (*see* Adjudication of events)

#### Baseline characteristics

Vital signsSymptomsECG

Attending doctor’s evaluation of severity after initial examination (doctor’s “gut feeling”): dichotomous: serious condition or not serious conditionTiming (symptoms, admission)Presumed MACE during and after index admissionDiagnostic procedures during and after index admissionBiochemistry results during and after index admissionInterventions performed during and after index admissionAdditional admissions after index admission

### Adjudication of major adverse cardiac events

The components of the primary outcome (MACE endpoints and time of MACE endpoints) are adjudicated via a combination of auto-adjudication and manual adjudication.

#### Auto-adjudication

A subset of the events are so extensively documented in the mentioned registries and databases that an automatic adjudication has been accepted by the endpoint committee. To further validate this procedure, at least 10% of all automatic adjudications are subsequently confirmed by the endpoint committee.

#### Manual adjudication

The manual adjudication is performed by an independent endpoint committee consisting of six to nine (depending on the final number of suspected events; *see below*) Danish independent cardiologists from outside the Central Denmark Region (*see* Additional file 4). Because of the high level of completeness and quality of the Danish health care registries and available electronic databases, a complete review of medical records from all patients is not considered to be necessary. Instead, only selected suspected events are presented to and evaluated by the endpoint committee (*see below*). Each suspected event is independently evaluated by two cardiologists. The adjudication is based on patient medical records, laboratory results and other supplementary information on request from the adjudicators. The endpoint committee is, per protocol, blinded to randomization status; the assigned group may be derived de facto from the medical record in most cases. All other information is available in the adjudication process.

All-cause death is accepted if the patient is registered as dead in the social security register. Survived cardiac arrest is accepted if a resuscitation attempt by a health care professionals is registered in the patient medical record and the patient survived to discharge. Non-scheduled re-vascularizing coronary intervention (PCI or CABG) is accepted if a non-scheduled coronary re-vascularization is registered in the patient medical record. Life-threatening, treatment-demanding arrhythmias are accepted if third-degree atrioventricular block, ventricular tachycardia or ventricular fibrillation resulting in initiation of treatment is registered in the patient medical record. Re-admissions with ACS (including NSTEMI types 1–5, STEMI types 1–5 and UAP) are accepted according to the criteria described in the Universal Definition of AMI (*see* Additional file 4 for full description). Myocardial injury is adjudicated by the endpoint committee but is not included as part of the endpoint of re-admissions with ACS.

The adjudication is documented in TrialPartner by each adjudicator, and the event is confirmed if both adjudicators agree. In case of disagreement between the two reported adjudications, the event is evaluated by a third member of the endpoint committee (*see* Additional file 4).

#### Suspected events

A pre-adjudication is performed before endpoint committee assessment. Suspected events are automatically identified from all available data (*see* “Data materials” section) using STATA15 IC statistical/data management software (StataCorp, College Station, TX, USA).

Suspected events and automatic adjudication are defined for each possible endpoint of MACE. *See* the complete description of suspected events, MACE adjudication and automatic adjudication in Additional file 4.

#### Retention

Because the patients’ part of this study is completed as soon as a diagnosis of AMI is confirmed or rejected during index admission, there is no need for participant retention plans. The Danish health care registries are of high quality and have a high rate of completeness. Data will be analysed on both an intention-to-treat and per-protocol basis to accommodate issues of protocol non-compliance/deviation.

